**Fig. 3 Fig3:**
[figure not shown]
Likert-like questionnaire

Concerning complications, the number of wound healing complications, haematomas, anterior knee pain, periprosthetic fractures, deep infections, aseptic loosening, deep vein thromboses, and surgical revision will be collected at discharge and each follow-up.

### Surgical procedures and rehabilitation protocol

All patients shall receive a 1.5 g single administration of intravenous cefuroxime at induction of anaesthesia. A femoral nerve block shall be used for pain control and maintained for 48 h. A tourniquet 120 mmHg over the systolic arterial pressure shall be used. All surgeries will be performed using a standard medial parapatellar approach. A restricted kynematic alignment will be performed to all TKA. All components will be implanted following manufacturer instructions using the Smith & Nephew Legion Genesis II, with a posterior stabilised polyethylene liner insert. Both femoral and tibial implants will be cemented using Palacos cement (Heraeus Medical GmbH, Wehrheim, Germany). At the end of the procedure, 1 g of tranexamic acid will be injected intra-articularly. One closed suction deep drain and one open suction subcutaneous drain shall be used for the first 48 h. Anti-thrombotic prophylaxis with Rivaroxaban, 10 mg daily for 6 weeks, will start 12 h after the index procedure. Physiotherapy will follow standard protocols [21]. Patients will be followed by a team of physiotherapists during hospitalization from the first postoperative day. In the absence of complications or other medical reasons who prevent discharge, the standard length of hospitalisation at our institution is 5 days. Moreover, from POD-2, each patient will undergo two sessions of physiotherapy daily using continuous passive motion (CPM) for 60 min per session to flex and extend the knee joint. The physiotherapist will increase the range of motion at each. Patients shall be discharged when they shall have reach at least 80° of flexion. Starting from POD-2, patients will start to walk under physiotherapeutic supervision, and on POD-4 they shall start to ascend and descend stairs. A personalised outpatient or inpatient rehabilitation program will be set for every patient for a minimum of 3 weeks. Deviation from the planned surgical procedure and rehabilitation protocol shall warrant exclusion from the study.

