### Randomisation and blinding

The present study is a protocol for a single-blind randomised controlled trial in which each group of participants is exposed to only one of the study interventions. Patients will be randomly allocated to robotic-assisted TKA or to conventional freehand TKA. All patients in whom a TKA is indicated will be sequentially allocated in a 1:1 ratio to surgeons who perform robotic-assisted TKA or to those who perform conventional freehand TKA at the time of their outpatient appointment. All patients, irrespective of their allocation, will follow the same clinical, imaging, and anaesthesiologic pre- and post-surgical pathways. Patients will be blinded to the allocation until the first postoperative days. Surgeons and personnel involved in the clinical management of the patients will be unblinded to the allocation. Data curacy and collection will be conducted by two assessors blinded to group allocation and not involved in the clinical management of the patients. Assessors will retrieve patient data at the following follow-up times: admission, perioperatively (from access to discharge), at 6 weeks, 12 months, and every 24 months postoperatively. Data from patients will be collected once the learning curve has been reached.

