Data from patients will be collected once the learning curve has been reached. The learning curve represents the relationship between how proficient surgeons will be in the performance of robotic TKA and the amount of experience they have. Data on the surgical duration will be collected. Surgical duration is considered as the minutes elapsed from incision to complete suture of the wound. The learning curve is considered the number of robotic TKA necessary to reach a plateau in the curve of the surgical duration. The plateau in surgical time implies that the surgeons’ skills do not improve substantially with each further operation, with less new expertise gained. Robotic TKA using CORI is believed to reduce surgical time. The CORI software offers a surgical workflow which improves efficiency and ease of use, further shortening the learning curve, with a 72% reduction in required data point collection with automatic landmark capture, 40% fewer work steps, faster surface model generation, and a 29% faster bony resection [26]. The evidence on the learning curve of robotic TKA is limited, and the literature would benefit from further investigations. However, the learning curve is dependent on assumptions made about performance, and many variables impact learning and future performance. The predictive value of the learning curve to predict the overall performance of larger groups should be considered with caution, as the assumptions are made on heterogeneous variables, including surgeon motivation, workplace dynamics, and training resources. Further investigations should clarify the learning curve of robotic TKA using CORI and whether previous knowledge or experience impacts the learning curve.

Accurate pre-operative planning to determine the correct implant size and position is an important aspect which supports the surgeon pre- and peri-operatively. It is regarded as a vital step to successful component implantation, which may increase implant survival and reduce complications associated with surgery [27, 28]. Furthermore, pre-surgical templating is also important from an economic point of view, as a correct estimation of component sizes can avoid the waste of expensive components. However, it is unclear whether robotic TKA will produce greater accuracy in preoperative planning, and clinical investigations are missing.

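### Patients who deviate from the surgical or rehabilitation pathway are excluded after allocation, so the comparison may be biased by an unknown amount in an unknown direction

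*Protocol article*

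**What the plan says.** The protocol article, under 'Surgical procedures and rehabilitation protocol', sets out one pathway for all patients. It fixes the approach, implant, cement, drains, physiotherapy, continuous passive motion from the second postoperative day and at least three weeks of rehabilitation. Among the steps is "Starting from POD-2, patients will start to walk under physiotherapeutic supervision, and on POD-4 they shall start to ascend and descend stairs". The section closes with "Deviation from the planned surgical procedure and rehabilitation protocol shall warrant exclusion from the study".

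Under 'Randomisation and blinding', patients are "sequentially allocated in a 1:1 ratio to surgeons who perform robotic-assisted TKA"; the other arm goes to surgeons who operate freehand. This is done at the outpatient visit, so allocation precedes admission, surgery and rehabilitation. The same section states: "Surgeons and personnel involved in the clinical management of the patients will be unblinded to the allocation". Data are collected by two blinded assessors who take no part in clinical management.

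'Statistical analysis' specifies unpaired t-tests and chi-squared tests of a no-difference null. It does not say that all allocated patients are analysed in their allocated group, and no other section does.

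**The concern.** A rule that removes patients for something that happens after allocation leaves groups that are no longer the allocated groups. The balance that allocation provides is then not guaranteed in the patients analysed.

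The deviations in question can plausibly be tied to outcome. A robotic operation completed freehand departs from the planned procedure, and the conventional arm has no matching event. A patient whose complication prevents walking on the second day or stairs on the fourth departs from the rehabilitation schedule. The outcomes at stake are the patient-reported scores, range of motion, length of stay and complications. The staff placed to observe a deviation know the arm.

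The rule excludes from the study, not from a per-protocol set. Read plainly, follow-up of these patients may end, and an analysis plan written later could not recover outcomes that were never collected. The rule also sits badly with the aim in the Discussion, which is to evaluate the introduction of robotics in routine practice.

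**Working it through.** **Order of events.** Allocation is at the outpatient appointment; surgery and rehabilitation come later. A deviation from either can only occur after allocation, so every exclusion under the rule is a post-allocation exclusion.

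**The plan's own figure.** 'Sample size evaluation' gives a difference of 5 units, SD 20, 80% power, 5% significance and 198 per group. With a one-sided 5% test, n = 2 × (1.645 + 0.842)² × 20² / 5² = 197.8, hence 198. The figure reproduces. The text mentions no allowance for exclusions.

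**Bias formula.** Let qR and qC be the shares excluded in the robotic and conventional arms. Let g be the amount by which excluded patients score worse than retained patients in the same arm. The mean of the retained patients is better than the whole-arm mean by q × g. With the same g in both arms, the difference among retained patients is therefore shifted by

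bias = (qR − qC) × g,

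where a positive value favours robotic surgery. The article gives neither q nor g, so all values below are assumptions.

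| Excluded, robotic / conventional | g = 10 points | g = 20 points |
|---|---|---|
| 5% / 5% | 0 | 0 |
| 10% / 5% | 0.05 × 10 = 0.5 | 0.05 × 20 = 1.0 |
| 15% / 5% | 0.10 × 10 = 1.0 | 0.10 × 20 = 2.0 |
| 5% / 10% | −0.5 | −1.0 |
| 5% / 15% | −1.0 | −2.0 |

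Against the planning difference of 5 points, 0.5 is 10% and 2.0 is 40%.

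Equal shares protect only if the deficits are also equal. With 10% excluded in each arm but deficits of 20 and 10 points, the bias is 0.10 × 20 − 0.10 × 10 = 1.0 point.

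**Effect on the error rate.** Take no true difference, 198 allocated per arm, SD 20 and a two-sided 5% test of the stated null (normal approximation).

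- 5% / 5%: no bias, and the type I error stays at 5.0%.
- 10% / 5%, g = 10: the standard error is 20 × √(1/178.2 + 1/188.1) = 2.09, bias over standard error is 0.24, and the type I error is 5.7%.
- 15% / 5%, g = 20: the standard error is 20 × √(1/168.3 + 1/188.1) = 2.12, the ratio is 0.94, and the type I error is 15.6%.

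Reversing the shares gives the same error rates with the excess in favour of conventional surgery.

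**The case against.** The strongest reply is that the article does not say what its critic fears. It does not state that a complication counts as a deviation. It expects complicated recoveries within the pathway, since the five-day stay applies only when no complication or other medical reason prevents discharge. Complications are collected at every follow-up, and one that arises after rehabilitation has ended cannot be a rehabilitation deviation. The later rehabilitation is personalised, which leaves room for variation. All this stands. It limits the point to a plausible link between deviation and outcome. It does not supply a safeguard.

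Five stronger readings are tempting, and the text does not support them.

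- A reader might infer that the rule removes the worst outcomes or destroys the comparison. That depends on which patients are excluded and how the arms differ, and the article does not let one compute it.
- A reader might infer that unblinded staff decide on exclusion. The article says only that clinical staff know the allocation, not who decides.
- A reader might count slow recovery of flexion as a route to exclusion. Under the discharge criterion such a patient simply stays longer, which complies with the pathway and shows up in length of stay.
- A reader might add the learning-curve start rule, "Data from patients will be collected once the learning curve has been reached", as a further exclusion from the robotic arm alone. That sentence is not limited to one arm and can be read as a run-in for both. How the start is determined is a separate question.
- A reader might stress lost power. On the one-sided test that reproduces 198, an assumed 10% exclusion lowers power from 80.0% to 76.3%. With about 2000 knee replacements a year at the centre, the numbers look replaceable. Extra recruitment would restore power but would not remove the bias.

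Finally, an analysis plan that is not shown may define an all-allocated analysis. It could do so only for patients whose data still exist.

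**Conclusion.** The exclusion sentence is wrong as written. It prescribes post-allocation exclusion from the study, and nothing in the article offsets it. The between-arm comparisons may be biased, with size and direction unknown.

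The illustrated WOMAC range of −2.0 to 2.0 points, including zero, rests on assumed exclusion shares of 5–15%, an assumed deficit of 10–20 points and, for the zero, equal deficits in the two arms. It shows that a modest imbalance could matter beside a 5-point planning difference. It is not an estimate of what will happen. No comparable figure is offered for range of motion, length of stay or complications.

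The point should be settled before the rule is applied further, because outcomes not collected from excluded patients may be unrecoverable.

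**What to change.** Replace the sentence with: *All allocated patients are followed and analysed in the group to which they were allocated, whatever deviation occurs; deviations are recorded. A per-protocol analysis is supportive only.*

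This is a one-sentence amendment and alters no step of the surgical or rehabilitation pathway. It costs the follow-up of patients who deviate and the recording of their deviations. The estimated effect may be slightly diluted, because a robotic case completed freehand counts in the robotic arm. That estimate fits the stated aim of evaluating robotics in routine practice, and the supportive per-protocol analysis still shows the result in patients treated as planned.

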### Outcomes of interests

The primary outcome of interest is to compare robotic-assisted TKA using CORI robotic system versus conventional freehand arthroplasty. The surgical duration, length of the hospitalisation, blood analyses, implant positioning, blood units transfused, ROM, PROMs, and complications will be collected from both groups and compared as shown in Fig. 1.

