## Discussion

Changes in surgical technique in experienced surgeons are always a challenge. The advantages of robotic surgery over conventional freehand TKA are still unclear, and evidence is missing. Therefore, the present randomised controlled trial wishes to evaluate the effect of the introduction of robotics in the arthroplasty of the knee in a routine clinical setting. According to the manufacturer, CORI is an intelligent platform which supports robotics, software, intelligent tools and data, and surgeon-controlled imageless intelligence with fast mapping. CORI delivers real-time planning and joint space assessment to improve soft tissue balance. CORI is believed to promote high accuracy of bone resection and implant alignment, reducing variation in component position [23–25]. However, these features have not yet been validated in clinical practice, and evidence is lacking.

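### Excluding patients who deviate from the surgical or rehabilitation protocol removes allocated patients because of the recovery and complications the trial compares

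*Protocol article*

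**What the plan says.** Under Randomisation and blinding, patients are allocated 1:1 at the outpatient appointment, before surgery. Surgical procedures and rehabilitation protocol then sets out a timed course common to both arms. There are two continuous passive motion sessions a day from POD-2, and mobilisation is fixed by day: "Starting from POD-2, patients will start to walk under physiotherapeutic supervision, and on POD-4 they shall start to ascend and descend stairs". Discharge requires at least 80° of flexion. After that, "A personalised outpatient or inpatient rehabilitation program will be set for every patient for a minimum of 3 weeks". The section closes: "Deviation from the planned surgical procedure and rehabilitation protocol shall warrant exclusion from the study".

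The only allowance for medical events in that section concerns length of stay: "In the absence of complications or other medical reasons who prevent discharge, the standard length of hospitalisation at our institution is 5 days".

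The outcomes include those that depend on early recovery. Outcomes of interests states that "ROM, PROMs, and complications will be collected from both groups and compared", alongside length of hospitalisation. The end of Data to be collected lists the complications to be counted: "the number of wound healing complications, haematomas, anterior knee pain, periprosthetic fractures, deep infections, aseptic loosening, deep vein thromboses, and surgical revision".

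**The concern.** The rule removes people from the study for what happens after allocation. Whether a patient manages passive motion and walking on POD-2 or stairs on POD-4 depends on how the knee is recovering, and that is what the trial sets out to compare. Several listed complications, when they occur early, can interrupt the schedule and so lead to removal of the patient who had them.

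If the arms differ in how often this happens, the groups analysed are no longer those formed at allocation. The arm that loses more poor recoveries looks better on WOMAC, range of motion and complications and, indirectly, on length of stay. A difference between arms is plausible because care staff know the arm: "Surgeons and personnel involved in the clinical management of the patients will be unblinded to the allocation". Patients also learn it during the inpatient stay. The rule covers deviation from the planned surgery too, which is the part of care that differs by arm. Even if losses are equal, complication counts are understated and both arms look better than ordinary care would. The Discussion acknowledges performance and detection bias but not this selection.

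**Working it through.** **The protocol's own figure.** Sample size evaluation gives a distance of 5 units, SD 20, 80% power, a 5% level and 198 per group. With a one-sided 5% level, n = 2 × (1.645 + 0.842)² × 20² / 5² = 197.8, so 198 per group. (A two-sided 5% level gives 252.) The SD and the 198 are used below; the concern does not depend on how they were obtained.

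**Assumptions.** The protocol gives no deviation rates. Let x be the share excluded in an arm. Let r be the correlation between an underlying, normally distributed tendency to deviate and a worse WOMAC, the same in both arms. Take r = 0.2 to 0.5 and no true difference between arms.

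**WOMAC bias.** Removing the top share x of that tendency shifts the retained mean by r × 20 × φ(z)/(1 − x), where z is the upper x point of the normal distribution. The factor φ(z)/(1 − x) is 0.1086 at 5%, 0.1950 at 10% and 0.2743 at 15%.

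- Equal x in both arms: bias 0.
- 5% v 10%: 20 × (0.1950 − 0.1086) = 1.73; times r gives 0.35 to 0.86 points.
- 5% v 15%: 20 × (0.2743 − 0.1086) = 3.31; times r gives 0.66 to 1.66 points.

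**False-positive rate.** Retained numbers are 188 v 178 or 188 v 168. Allowing for the slight reduction in SD that exclusion causes, the standard error of the difference is 2.03 to 2.11. The two-sided 5% rejection rate is Φ(−1.96 + bias/SE) + Φ(−1.96 − bias/SE).

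| Excluded | r | Bias (points) | Share of 5 units | False-positive rate |
|---|---|---|---|---|
| 5% v 10% | 0.2 | 0.35 | 7% | 5.3% |
| 5% v 10% | 0.5 | 0.86 | 17% | 7.1% |
| 5% v 15% | 0.2 | 0.66 | 13% | 6.1% |
| 5% v 15% | 0.5 | 1.66 | 33% | 12.8% |

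With the SD held at 20, the two upper rates are 7.0% and 12.2%. A simulation of 10,000 trials for the last row gave a bias of 1.67 and a rejection rate of 12.6%. If r is instead the plain correlation between the yes/no deviation indicator and WOMAC, the factor becomes √(x/(1 − x)) and the biases rise to 0.42–1.04 and 0.76–1.91.

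**Complications, unequal exclusion.** Suppose 12 of 198 in each arm have a complication (6.1%, odds ratio 1.00), and 6 of these patients in one arm and 3 in the other are excluded for interrupted rehabilitation. What remains is 6/192 (3.1%) v 9/195 (4.6%), and the odds ratio is (6/186)/(9/186) = 0.67.

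**Complications, equal exclusion.** Suppose true rates of 10% v 5%, with a share k of patients with complications excluded in both arms. The analysed rate is p(1 − k)/(1 − pk). The risk difference falls from 5.0 points to 3.9 (k = 0.25), 2.7 (0.5), 1.4 (0.75) and 0 (1). The odds ratio is unchanged for k below 1, because both odds are multiplied by (1 − k), but it rests on fewer events.

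**The case against.** The strongest reply is that deviation is not defined and the rule may be meant narrowly, for patients who receive a different implant, approach or care package. The regimen bends to recovery in places: discharge waits for flexion, a stay beyond 5 days is foreseen, rehabilitation after discharge is individualised, and physiotherapy follows a cited standard that may allow pauses. Collecting complications, revision included, at every follow-up also sits poorly with excluding everyone who has one. This is a possible reading, but the text does not say it. The medical clause qualifies only the length of stay, and the inpatient steps are fixed by day. An undefined rule also leaves room for discretion.

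Second, data are collected by two assessors blinded to allocation, and nothing says who decides on exclusion. That stands: arm-dependent decisions are a risk, not something the protocol shows. But unblinded staff deliver the rehabilitation, so deviations themselves can differ by arm whoever records them.

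Third, the reach is limited. Late infections, fractures, loosening and revisions are not caught by a schedule covering the inpatient days and a minimum of 3 weeks, and a longer stay alone need not be a deviation. This stands, and the point is confined to events that interrupt the schedule.

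Fourth, the sizes are assumed. The low case, 5.3%, is close to nominal; set against the 10-point minimum important difference, the percentages halve; and the 0.67 has a 95% interval of about 0.23 to 1.91, so that example would not by itself be declared a difference. All true. The figures illustrate a mechanism and do not predict a result.

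Finally, an unseen analysis plan might define an intention-to-treat set. It could not recover outcomes never collected because patients had left the study.

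**Conclusion.** The concern holds: the sentence is wrong as written. It is an explicit post-allocation exclusion from the study, without a medical exception, and it is tied to the early recovery the trial compares. Neither the direction nor the size of the bias can be derived from the protocol. Under the assumed unequal exclusion of 5% v 10% to 5% v 15%, with r from 0.2 to 0.5, the WOMAC difference shifts by 0.35 to 1.66 points and the false-positive rate lies between 5.3% and 12.8%. Under equal exclusion the WOMAC difference is unbiased, but complications are undercounted. The rule also fits poorly with the Discussion, which says the trial "wishes to evaluate the effect of the introduction of robotics in the arthroplasty of the knee in a routine clinical setting", although the same section describes highly standardised surgery. Confidence is high about the rule and its mechanism, and low about how large the effect would be here.

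**What to change.** Replace the exclusion sentence with wording such as:

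> *Patients whose surgery or rehabilitation departs from the plan remain in the study, are followed at 6 weeks, 12 months and every 24 months, and are analysed in the arm to which they were allocated. Each departure is recorded with its date and reason.*

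An analysis restricted to patients without deviations can stay as a sensitivity analysis. Rehabilitation itself need not change.

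The cost is one sentence in the text and no additional visits, since the follow-ups are already scheduled. The protocol is already registered and ethics-approved, with recruitment planned from January 1, 2023, so the change needs a formal amendment and, where possible, recovery of data on anyone already excluded. Keeping deviating patients may dilute the difference between arms and slightly widen the SD. That is the price of estimating the effect under ordinary care.
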